### Trial treatment and regimen

#### Intervention arm—behavioural activation therapy

Behavioural activation (BA) therapy is a structured and individualised treatment which aims to increase people’s level of activity, particularly the frequency of pleasant or enjoyable events, in order to improve mood. Participants randomised to receive BA will be treated at their place of residence by an assistant psychologist at two centres or low-intensity psychological wellbeing practitioner (PWP) at one centre. They will be offered a maximum of 15 sessions of BA over 4 months, with an expected average of 10 sessions. Therapy sessions will be delivered face to face on an individual basis, at the participants’ residences and will last about 1 h. A BA treatment manual was developed for CALM based on the behavioural component of CBT for depression in stroke patients [22, 24], behavioural therapy with older people [47] and guidelines on conducting therapy with people who have aphasia [35, 47, 48]. For this trial, this therapy manual will be further revised to cover BA with stroke patients who do not have aphasia and will provide examples and practical guidance relevant to all stroke patients.

The intensity and duration of therapy is based on a study of CBT with stroke patients [24] and is informed by the CALM study in which participants received an average of nine 1-h sessions over 3 months [33]. Experience and criticism of the CBT trial [24] was that therapy was too short. The trial of BA for treating depression in primary care provided 12 sessions over 3 months [49] but this was not in a stroke sample and patients with communication and/or cognitive difficulties may require a longer duration of therapy. The duration of therapy has been increased from 3 to 4 months because the CALM study showed that it was difficult to complete sessions in 3 months due to non-availability of the participant and short-term illness. Extending therapy to 4 months will also allow flexibility to provide therapy visits to support maintenance, as might be provided in clinical practice. The number of therapy sessions will vary according to the needs of the individual and their progress in therapy. The intensity of treatment will be negotiated between the therapist and the participant, based on their progress in achieving their therapy goals.

Goals set during treatment to increase enjoyable activities will be tailored to the individual. BA also includes between-session tasks to practice exercises and increase activity levels. Behavioural treatment strategies focus on maximising mood-elevating activities. The process of BA involves identifying how the person currently spends their time, identifying activities that they would enjoy doing (this may include resuming previous activities, increasing current activity levels or introducing new activities) and setting goals to increase the number of enjoyable activities.

The BEADS therapy manual presents a programme of BA delivered across 10 sessions, although the number of therapy sessions that a participant has (up to a maximum of 15) will vary according to the needs of the individual, their progress in therapy and their abilities.Session 1: Introducing behavioural activation therapy for depression after strokeSession 2: Identifying and agreeing therapy goalsSession 3: Monitoring activity levelsSession 4: Identifying enjoyable activitiesSession 5: Activity scheduling: enjoyable activitiesSession 6: Activity scheduling: increasing activity levelsSession 7: Activity scheduling and increasing enjoyable activities: problem solvingSession 8: Reviewing previous goals and setting new goalsSession 9 Generalising behavioural activation strategiesSession 10: Reviewing skills and making plans

Behavioural therapy techniques in the BEADS therapy manual include

Activity monitoring: Identifying how participants spend their time to assess current activity level, what activities they enjoy and when activities could be carried out. Participants are given an activity diary or timetable to complete as a between session task. The complexity of the diary will vary according to the cognitive and communication abilities of the patient and will be available in a range of formats.

Activity scheduling: Planning in advance realistic activities and goals for the participant to complete each day, which increases the likelihood that activities will be carried out. The intention is to gradually increase activities, and therefore the amount of positive reinforcement received, in order to improve mood. Activities will be set according to the abilities and goals of the individual.

Graded task assignment: Breaking a large task into smaller, manageable steps provides the opportunity to practise tasks participants find difficult. For example, for someone who wants to go shopping, they would start by going to a familiar local shop where they know people already; this would then be extended to going to a larger shop which is further away.

At two of the study sites, the therapists will be an NHS employed assistant psychologist. These are psychology graduates who work under the supervision of a clinical psychologist. At the third study site, the therapist will be a low-intensity psychological wellbeing practitioner who will have completed an accredited postgraduate certificate to qualify them as a psychological wellbeing practitioner. The therapists will attend a 2-day training workshop on BA led by an NHS consultant clinical psychologist and the chief investigator. The workshop will also include training from a speech and language therapist on communicating with stroke patients with cognitive and/or communication difficulties. Weekly clinical supervision for the therapists will be provided by a local clinical psychologist at each centre. In addition, the therapists will have a monthly teleconference with the chief investigator and NHS clinical psychologist.

#### Control arm—usual care

Participants in the usual care group will follow the current care pathway. Participants will receive all other services routinely available to them as local practice but will have no contact with the trial therapist. This group is the control arm and their care will be recorded to document usual care to inform the design of the definitive trial. Stroke survivors are admitted to hospital, usually to a stroke unit. On discharge, they may receive input from an early supported discharge team or input from a community stroke or rehabilitation team. Availability of psychological support in the community is inconsistent and likely to vary widely across the country as highlighted by the Stroke Improvement Programme [50]. The CALM trial [33] found that at the 3-month follow-up, only 14 % of participants had received mental health treatment in the past 3 months (from a mental health nurse, counsellor, psychologist or psychiatrist) and this decreased to 10 % at the 6-month follow-up. Although Improving Access to Psychological Therapies (IAPT) have extended their remit to include people with physical health problems [51, 52] the current rate of uptake by stroke patients is unknown.

Only patients not currently receiving psychological intervention are eligible to be recruited to BEADS. The provision of clinical psychology varies. Some sites have a full-time clinical psychologist providing input to both hospital and community services and other sites can access this service but do not have dedicated provision. IAPT services will consider treating stroke patients if referred, but this rarely occurs. GPs may prescribe anti-depressants. Only those with severe mental health problems are referred to psychiatrists. The content of usual care is decided locally by the clinical team as to what this will be, as per local services.

#### Intervention fidelity

To ensure the fidelity of the intervention, the content of treatment will be described and analysed. This will be achieved by video recording up to 24 intervention sessions, eight at each of the three centres. Participants and sessions will be selected iteratively using purposive sampling to represent the range of severity of depression (mild, moderate, severe from baseline scores) and across the phases of therapy (beginning, middle and end). Practices for video recording will draw upon guidance on minimising intrusiveness of the recording [53, 54]. The assessors analysing the videos will apply a customised therapy record form designed to capture a variety of key elements spanning all aspects of the intervention. Should a participant decline video recording, they will be offered audio recording instead. Participants will not be excluded from the study if they do not want to be video or audio recorded.

The therapists will also keep treatment notes for each session to summarise the content of the intervention, and to record goals set during BA and whether these were achieved. Therapists will also complete a record form of therapy content per session. The record form will quantify the content of the intervention (for example, how much time in each session was spent on different components). The record form will be based on a time sampling sheet adapted from that used in the CALM study and based on the content of the BA manual for this study. There will be triangulation between the videos, therapy record form and manual.

Qualitative interviews will be conducted with 16 participants (eight per arm), 10 carers (five per arm), and all three therapists by an independent researcher to provide a description of the acceptability of the design and procedures used in the trial and the BA intervention. All participants who participate in an interview will provide informed consent to do so. Participants will be selected iteratively using purposive sampling to represent participants from all three centres, the range of severity of depression (from baseline scores) and representation of stroke survivors with and without aphasia. All interviews will be audio recorded.

#### Patient-centred outcomes

In addition to the feasibility outcomes, the primary clinical outcome measure at 6 months is the PHQ-9 [39]. For those participants with moderate to severe language problems who are unable to complete the PHQ-9, the Visual Analog Mood Scales (VAMS) Sad item [40] will be used—this is a single-item visual analog mood measure. The number of participants unable to complete the PHQ-9 will be recorded, and the VAMS Sad will be completed with all participants so the relationship between the two measures can be explored.

The following measures will also be used to assess outcomes at 6 months:Stroke Aphasic Depression Questionnaire—Hospital version (observer-rated depression) [55]Nottingham Leisure Questionnaire (leisure activities) [56]Nottingham Extended Activities of Daily Living (functional outcome) [57]Carer Strain Index (carer-rated level of strain) [58]EuroQol EQ5D (health-related quality of life)—standard version [59] and picture-based version intended to be accessible for people with cognitive problems [60] for patients and carers (and proxy version)Healthcare resource use questionnaire

#### Sample size calculation

As a feasibility study, this is not powered for efficacy and no formal interim analyses of efficacy are planned. Rather, the sample size for a feasibility study should be adequate to estimate the uncertain critical parameters (standard deviation for continuous outcomes; consent rates, event rates, attrition rates for binary outcomes) needed to inform the design of the definitive RCT with sufficient precision. The sample size of 60 patients allows standard deviation for continuous outcomes, such as the PHQ-9 and VAMS Sad, to be estimated to within precision of approximately ±19 % of its true value (with 95 % confidence). Allowing for 15 % attrition by 6-month post-randomisation follow-up, 72 participants need to be recruited. To achieve the target sample size of 72, over the 12-month recruitment period, with three centres we need to randomise two participants per centre per month.

#### Data analysis

All trial analyses will be conducted according to an a priori statistical analysis plan that will be prepared during the early stages of the trial in agreement by the Trial Management Group, Trial Steering Committee and the Data Monitoring and Ethics Committee. Primary analysis will be conducted on the intention-to-treat population; however, exploratory analysis may be conducted excluding patients who do not comply with the protocol.

As the trial is a pragmatic parallel group, the data will be reported and presented according to the CONSORT 2010 statement [61]. As a feasibility study the main analysis will be descriptive and focus on confidence interval estimation and not formal hypothesis testing and will be guided by the Thabane et al. (2010) checklist for reporting of pilot trials [37]. Rates of consent, recruitment and follow-up by centre and by randomised group will be reported. Outcome measures will be summarised overall and by randomised group, to inform sample size estimation for the definitive trial. The data from this feasibility study will be used to estimate the consent rate, attrition rate and the variability of the continuous outcomes in the trial population and use this information to inform the sample size calculation for the definitive RCT. Study site will be treated as a covariate in an adjusted analysis where we estimate the treatment effect adjusted for baseline score and site. Since the intervention is therapist led, the data will be used to estimate the intra-cluster correlation coefficient for patients treated by the same therapist using a marginal or random effects model for the 6-month post-randomisation PHQ-9 outcome.

As part of the feasibility analysis, the effect size for the 6-month PHQ-9 outcome and the difference in mean scores (and associated 95 % confidence intervals [62]) between groups will be estimated. A marginal or random effects model will be used to allow for any clustering by therapist, with baseline PHQ-9 as a covariate to check that the likely effect is within a clinically relevant range, and this will be used as confirmation that it is worth progressing with the definitive trial. The accuracy of the cut-off of the VAMS Sad in comparison with the PHQ-9 will also be checked. This information along with the acceptability of the study design and protocol to patients and carers; the safety of the intervention; patient recruitment and consent/retention rates will enable us to determine whether or not the definitive RCT is feasible.

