More specifically, if during the trial there is a patient allocated to the BEADS intervention who subsequently needs clinical psychology input (as per the protocol of the local service) then the BEADS therapist (AP/PWP) will discuss this with the clinical psychologist or clinical lead and the patient and will agree what is best for the patient. If it is agreed that the patient needs immediate clinical psychology input then they would be withdrawn from the BEADS intervention and they will see the clinical psychologist, or be referred to alternative provision, as appropriate to that patient. The patient will be withdrawn from the intervention but not the overall trial, i.e. we will still be able to collect outcome data from them. We will record the number of patients who we withdraw from the BEADS intervention because of a conflict with clinical services.

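### Excluding non-compliers would fall mainly on the BA arm and break the randomised comparison; an allocation-based analysis of receiving BA would avoid this at little cost

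*Protocol article*

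**What the plan says.** All places are in the protocol article; the statistical analysis plan is not shown.

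- **Data analysis.** "Primary analysis will be conducted on the intention-to-treat population". The same sentence adds that "exploratory analysis may be conducted excluding patients who do not comply with the protocol". The article also states that "All trial analyses will be conducted according to an a priori statistical analysis plan" and that "the main analysis will be descriptive and focus on confidence interval estimation and not formal hypothesis testing". It does not define compliance.
- **Intervention arm—behavioural activation therapy.** "They will be offered a maximum of 15 sessions of BA over 4 months, with an expected average of 10 sessions". No minimum is set: "The number of therapy sessions will vary according to the needs of the individual and their progress in therapy".
- **Control arm—usual care.** "The content of usual care is decided locally by the clinical team". The only visible restriction on a control patient is that there is no contact with the trial therapist.
- **Informed consent.** For patients allocated to BA, "If it is agreed that the patient needs immediate clinical psychology input then they would be withdrawn from the BEADS intervention". These patients stay in the trial and their outcomes are still collected. The same section lists general reasons for withdrawal, including not adhering to the protocol, for participants in both arms.

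**The concern.** Although optional, the clause names a method: patients are removed after randomisation according to what they did. In this design that is close to one-sided. A BA patient can stop early, miss sessions or be moved to another service. A usual-care patient with the same prognosis and the same tendency to drop out of therapy cannot be identified and stays in the analysis. Selected BA patients are then compared with nearly all controls.

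The selection could well be related to outcome. Patients judged to need immediate clinical psychology plausibly have a worse outlook, and the number of sessions depends on progress, which is itself a response to treatment. Defining compliance in the analysis plan would make the rule reproducible. It would not restore comparability, because the imbalance comes from excluding patients, whatever the definition.

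What is at stake is interpretation. With no formal tests, readers will rely on the estimates, and one that leaves out non-compliers can be taken for the effect of BA in those who received it.

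**Working it through.** **The plan's own figures, for scale.** Sixty evaluable patients with 15% attrition gives 60/0.85 = 70.6, so 71. The stated 72 agrees with 3 centres × 2 per month × 12 months = 72. Equal allocation gives 36 randomised and about 30 evaluable per arm. The 95% half-width for a difference in means is then 1.96 × √(2/30) = 0.51 SD, before any gain from baseline adjustment.

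**Inputs that the article does not give (assumed).** The share *p* of the BA arm excluded; the correlation ρ between the tendency to be excluded and 6-month PHQ-9 (higher is worse); and the PHQ-9 SD.

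**Formula.** Suppose BA has no effect and the top fraction *p* on a normal tendency score is dropped from BA only. The apparent BA-minus-control difference in SD units is −ρ × φ(z₁₋ₚ)/(1−p). For 6 of 36 excluded, z = 0.967 and φ = 0.250, so the multiplier is 0.250/0.833 = 0.300.

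| Excluded from BA | Multiplier | ρ = −0.3 | ρ = 0 | ρ = 0.3 | ρ = 0.5 |
|---|---|---|---|---|---|
| 3 of 36 (8%) | 0.167 | +0.05 | 0 | −0.05 | −0.08 |
| 6 of 36 (17%) | 0.300 | +0.09 | 0 | −0.09 | −0.15 |
| 9 of 36 (25%) | 0.424 | +0.13 | 0 | −0.13 | −0.21 |
| 30% | 0.497 | +0.15 | 0 | −0.15 | −0.25 |

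Negative values favour BA. A simulation of the first three rows agrees to within 0.01 SD. At ρ = 0.7, a strong assumption, 9 of 36 excluded gives −0.30.

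**If controls are excluded too.** At ρ = 0.5, dropping 6 of 36 from BA and 3 of 36 from control gives −0.5 × (0.300 − 0.167) = −0.07. Equal exclusion by the same mechanism in both arms gives 0. The size therefore depends on how one-sided the exclusion is.

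**In context.** The range 0.05 to 0.25 SD is 10% to 49% of the 0.51 SD half-width. If the PHQ-9 SD is 5 to 6, it is about 0.25 to 1.5 points (0.05 × 5 to 0.25 × 6).

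**The alternative.** Controls do not meet the trial therapist, so the instrumental-variable estimate is roughly the intention-to-treat difference divided by the proportion receiving BA. At an assumed 80% receipt, estimate and interval both scale by 1/0.8 = 1.25.

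**The case against.** The strongest reply is that the clause is optional, exploratory and undefined. Intention-to-treat is primary, inference is descriptive, and a condensed article properly leaves the compliance population to the analysis plan. All of that stands. It limits how much the point matters, and the missing definition is not itself a fault.

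Three stronger readings are tempting and are not supported:

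- *That the analysis is biased towards BA by construction.* The sign depends on who is dropped. Since session number follows progress, patients who improve and finish early could be the ones removed, which would bias against BA. Patients who recover under clinical psychology would act the same way.
- *That patients withdrawn from BA for clinical psychology are among those excluded.* The article prescribes that withdrawal and keeps collecting outcomes, so it can equally be read as following the protocol. Nor are exclusions certain to be confined to BA, because the general withdrawal reasons are worded for everyone.
- *That the decision to proceed rests on this analysis.* The Data analysis section uses the 6-month PHQ-9 effect to confirm that a definitive trial is worthwhile, but does not tie that check to a compliant subset. It also weighs acceptability, safety, recruitment and retention.

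A further objection is that an instrumental-variable analysis is not assumption-free. That is right. It is consistent rather than unbiased, and a threshold above one session would class partly treated patients as untreated and inflate the estimate. The definition of receipt has to avoid this.

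The objection to the method survives. The article names exclusion, and in this design exclusion does not give a randomised comparison under any workable definition that turns on taking part in BA.

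**Conclusion.** The point holds as an inexpensive improvement to one optional exploratory analysis. Excluding non-compliers would fall mainly on BA, because usual care has almost no regimen to breach, and the result would not be a randomised comparison. It would be biased if non-compliance is related to outcome. Under the assumed values the bias is about 0.05 to 0.25 SD towards BA if patients with a worse prognosis are dropped, nil if exclusion is unrelated to outcome, and reversed if early improvers are dropped. A bias towards BA is the likelier direction, but that is a judgement and not something the article establishes. The exclusion rate, the correlation and the PHQ-9 SD are all assumptions. The intention-to-treat analysis is unaffected.

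**What to change.** Replace the exclusion clause in Data analysis with wording such as:

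> Randomised patients will not be excluded for non-compliance; any exploratory analysis of the effect of receiving BA will use randomised allocation as an instrument, adjusted for baseline PHQ-9 and centre, with receipt defined before outcomes are seen as any BA session attended, or as number of sessions.

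This also removes the need to decide whether patients withdrawn from BA count as non-compliers. No new data are needed: Intervention fidelity has therapists keep notes and a record form for each session, and outcomes are still collected after withdrawal from the intervention.

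**Costs.** The interval is about 1.25 times the intention-to-treat half-width at 80% receipt. The estimate is consistent only if allocation acts solely through the BA received. Defining receipt as any session attended protects that assumption best, but if nearly everyone attends once the answer will be close to intention-to-treat. The dose version uses more of the session data but also needs the effect to be linear in sessions.
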